### Sample size calculation (cfr 4.4 Sample size)

**Sample size for measuring difference in sleep quality measured by RCSQ between intervention and control group**

Sample sizes of 99 in group SG and 99 in group WG which were obtained by sampling 3 clusters with an average of 33 subjects each in group one and 3 clusters with an average of 33 subjects each in group two, achieve 80% power to detect a difference on the RCSQ between the group means of at least 7.7. We have obtained this difference from a study using RCSQ to assess the relation between sleep and delirium prevalence(23). The standard deviation of subjects is 10.27. The intracluster correlation coefficient is difficult to predict so we have chosen to be on the safe side by choosing 0.030. The coefficient of variation of cluster sizes is 0.000. A two-sided t-test was used with a significance level of 0.050. This test used degrees of freedom based on the number of clusters.

In conclusion:

Medical patients:

Intervention (WG): 99

Control group (SG): 99

Surgical patients:

Intervention (WG): 99

Control group (SG): 99

Total: 396 patients.

**Sample size EEG headband**

We chose sleep efficiency as our primary outcome on the substudy with EEG-headbands. There are no studies using either the Philips or Dreem Headband to compare sleep in two groups. However, polysomnography (PSG) also uses an EEG signal. One study studying sleep parameters using PSG compared groups before either a low or high dose of melatonin, and found a statistical significant difference of 6.24 with a standard error of 1.81 (24). This yields a sample size of 3 in each group, using an unpaired t-test with a power of 80% and significance level of 0.05.

## Secondary study parameter(s)

- Night-to night changes in subjective sleep quality as measured with the RCSQ. To compare this a repeated measures ANOVA will be performed.
- Difference in subjective sleep quality between hospital and at home. For this outcome, we will assess the subjective sleep quality at home retrospectively at inclusion. To compare this a paired t-test with a significance level of 0.05 will be performed.
- Diurnal phase shift of sleep-wake timing: The phase shift of sleep-wake timing will be assessed by comparing midpoint of sleep during admission with midpoint of sleep on a work-free day before admission, both measured with the Consensus Sleep Diary (CSD). For this outcome, we will assess sleep-wake timing at home retrospectively at inclusion. To compare this a paired t-test with a significance level of 0.05 will be performed.
- Night-to-night changes in sleep-wake timing: The changes in sleep-wake timing (i.e. midpoint of sleep, sleep on- and offset time, sleep duration, sleep latency & inertia and daytime napping), as measured by the CSD. To compare this a repeated measures ANOVA will be performed.
- Timing of food intake and sleep quality/timing: the association between food intake timing (i.e. first and last meal of the day and whether food was eaten after 21:00h), as measured by asking patients directly for the time of the first and last meal of the day and whether patients ate after 21:00h), and subjective sleep quality and sleep-wake timing (as measured by the Richard Campbell Sleep Questionnaire. A linear regression will be performed for food timing as continuous variable, and a logistic regression will be performed for food timing after 21.00h as dichotomous variable.
- Quality of recovery (for surgical patients) and sleep quality/timing. The association between quality of recovery (in surgical patients), as measured by the Quality-of-Recovery 15 item questionnaire (QoR-15), and subjective sleep quality and sleep-wake timing (as measured by the Richard Campbell Sleep Questionnaire and Consensus Sleep Diary respectively). The QoR-15 will be completed twice by patients. A linear regression will be performed.
- 30 day mortality, assessed by checking the medical record retrospectively 30 days after admission. This will be compared between the intervention and control group by performing a Chi-square test.
- 30-day incidence of delirium during admission, as assessed by a physician during admission. Patients will be assessed for delirium at the request of nursing staff or if the score of the Delirium Observation Screening scale is 3 or higher. The Delirium Observation Screening scale ranges from 0 to 39, with higher scores indicating a higher chance of delirium. This incidence will be compared between the intervention and control group by performing a Chi-square test.
- 30-day incidence of surgical site infections (for surgical patients), as assessed by physicians from the department where patient is admitted during hospitalization. If the patient obtained a surgical site infection after discharge, incidence was assessed in the outpatient clinic by a physician from the department where patient was admitted. This will be compared between the intervention and control group by performing a Chi-square test.

Objective sleep substudy:

- Sleep efficiency (objectively measured) during admission. Objective sleep quality will be measured by the Dreem-3 headband, using electro-encephalography (EEG) to differentiate between wakefulness, Rapid-Eye-Movement (REM) sleep and non-REM N1, N2 and N3 sleep. The primary outcome measure will be sleep efficiency (time slept divided by time in bed spent trying to sleep), compared for patients on intervention and control departments. If data are distributed normally, an unpaired two sided t-test with a significance level of 0.050 will be performed to compare the sleep quality of the intervention group with the control group. If data are not normally distributed, the equivalent non-parametric test will be used.
- Differences in objective sleep measures of sleep-wake timing during admission. Changes in sleep-wake timing (i.e. midpoint of sleep, sleep on- and offset time, sleep duration, sleep latency & inertia) will be compared for patients on intervention and control departments. If data are distributed normally, an unpaired two sided t-test with a significance level of 0.050 will be performed to compare the sleep quality of the intervention group with the control group. If data are not normally distributed, the equivalent non-parametric test will be used.
- Night-to-night changes in objective sleep measures during admission. To compare this a repeated measures ANOVA will be performed.
- Difference between objective and subjective sleep measures during admission. Subjective sleep measured with the RCSQ and CSD. This will be evaluated by looking at the association between objective and subjective sleep by performing linear regression.
- Quality of recovery after surgery and objective sleep quality/timing. This will be evaluated by performing linear regression.
- Correlation 30 day mortality and objective sleep quality/timing. This will be evaluated by performing linear regression.
- Correlation 30-day incidence of delirium during admission and objective sleep quality/timing. This will be evaluated by performing linear regression.
- Correlation 30-day incidence of surgical site infections (for surgical patients) and objective sleep quality/timing. This will be evaluated by performing linear regression.

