## Secondary Objectives:

- To investigate whether the WEsleep interventions improves subjective sleep quality for all nights of admission (max. 7)
- To investigate whether the WEsleep interventions reduced the lowering of subjective sleep quality during admission when compared to subjective sleep quality before admission (on a work-free day 30 days before admission, retrospectively assessed at inclusion)
- To investigate whether the disruption of the circadian timing system (as measured by the diurnal phase shift of midpoint of sleep) was smaller for patients in the intervention group on the first postoperative night for surgical patients and the second night of admission for medical patients
- To investigate whether the WEsleep interventions reduced night-to-night changes in subjective sleep-wake timing (i.e. midpoint of sleep, on- and offset, duration, latency, inertia and daytime napping) for all nights of admission (max. 7)
- To investigate the association between the timing of food intake (i.e. first and last meal of the day and whether food was eaten after 21:00h) and sleep quality and timing.
- For Surgical patients: To investigate the association between quality of recovery and sleep quality and sleep-wake timing
- To investigate 30-day mortality for patients admitted into intervention and control departments
- To investigate 30-day incidence of delirium for patients admitted into intervention and control departments
- For surgical patients: to investigate the 30-day incidence of surgical site infections

Objective sleep substudy

- Objective sleep substudy: to investigate the difference between intervention and control departments in objective sleep efficiency of hospitalized patients on the second night of admission (in medical patients) and the first postoperative night on ward (in surgical patients) as measured by the Dreem-3 EEG-headband
- Objective sleep substudy: to investigate whether the WEsleep interventions reduced night-to-night changes in objective sleep-wake timing (i.e. midpoint of sleep, on- and offset, duration, latency, inertia and daytime napping) for all nights of admission (max. 7)
- Objective sleep substudy: to investigate whether the WEsleep interventions influence night-to-night changes in objective sleep measures (as measured by the Dreem 3 EEG-headband and Withings Sleep analyzer) for all nights of admission (max. 7)

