# STUDY DESIGN

In this cluster randomized controlled trial, performed in both locations of the Amsterdam University Medical Centre, we will randomize 6 surgical and 6 medical departments to either standard care group (SG) or WEsleep intervention group (WI). All adult patients admitted to the participating departments will receive the sleep improving interventions during their admission, informed consent will be obtained for sleep assessment.

Implementation of the interventions will be evaluated on a regular basis throughout the length of the study to make sure that all interventions are provided to our patients as planned. Before implementation, a baseline measurement will be conducted on all participating departments in a small number of patients (which is not part of the sample size). We observed that some interventions were gradually implemented. As such, we decided that for optimal assessment of the effect of the intervention a run-in period of 12 weeks before starting assessment of the primary and secondary outcomes would be reasonable. Sleep measurements between study onset and outcome will be used to guide implementation and will be reported in eventual journal articles.

After 12 weeks (that is, after July 1st), 33 patients per participating department will be included, for a total of 396 patients (12 departments with 33 patients each) and analyzed for the outcomes of the study. Informed consent for sleep measurements will be obtained on the first or second day of admission into one of the participating wards. Patients will be followed until discharge or for a maximum of 7 nights of admission. Patient characteristics, as well as data on the admission will be extracted from the electronic medical record. Patients will be asked to complete two questionnaires daily: Richards Campbell Sleep Questionnaire (RCSQ) on subjective sleep quality and the Consensus Sleep Diary (CSD) for day-to-day sleep wake timing. Furthermore, patients are asked at admission to complete the two questionnaires on sleep quality and sleep-wake timing on work- and work-free days (RCSQ and CSD) retrospectively, i.e. for 30 days before admission. Surgical patients will also complete a Quality of Recovery 15 (QoR-15) questionnaire twice (once at one day after surgery/first day of admission and once three days after surgery/third day of admission).

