## Inclusion criteria

In order to be eligible to participate in data collection for this study, a subject must meet all of the following criteria:

A) (elective surgery patients)

- Adult (18+) patients
- Undergoing elective non-cardiac surgery with planned (postoperative) overnight stay
- Willing and able to provide informed consent
- Able to read and write in Dutch

B) (medical patients)

- Adult (18+) patients on medical departments with expected stay of at least two nights.
- Willing and able to provide informed consent
- Able to read and write in Dutch

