### Time of other study parameters

Secondary endpoints will be measured during admission with a maximum of seven days. If a patient leaves the hospital before these seven days, the measurements will be stopped.

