**Study procedures**

After obtaining informed consent, patients are provided with the RCSQ and CSD for each day of admission, as well as for a regular night at home (one workday and one work-free day). Filled out questionnaires will be collected daily. Baseline characteristics and relevant data on admission (such as morbidity, length of hospital stay, etc.) will be collected from the patient records. Discharge from the hospital will be the end of the study for each participant.

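### Repeated-measures ANOVA is named for the night-to-night outcomes, although the number of nights per patient varies by design and the method needs a complete set

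*Protocol*

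**What the plan says.** **Method.** Section 10.2 (Secondary study parameter(s)) gives the same sentence, "To compare this a repeated measures ANOVA will be performed", for night-to-night RCSQ and for diary-based sleep-wake timing. It repeats it for the device measures in the substudy: "Night-to-night changes in objective sleep measures during admission. To compare this a repeated measures ANOVA will be performed".

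**Measurement period.** Study Design: "Patients will be followed until discharge or for a maximum of 7 nights of admission". Time of other study parameters: "If a patient leaves the hospital before these seven days, the measurements will be stopped". Study procedures: "Discharge from the hospital will be the end of the study for each participant".

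**Minimum stay.** Inclusion criteria, surgical: "Undergoing elective non-cardiac surgery with planned (postoperative) overnight stay". Medical: "Adult (18+) patients on medical departments with expected stay of at least two nights".

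**Target.** The Secondary Objectives ask about subjective sleep quality, sleep-wake timing and objective sleep over all nights of the admission, with a ceiling of seven.

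**Analysis set.** The opening of the Statistical Analysis section requires an RCSQ total on the primary outcome night only. It asks nothing of other nights.

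No passage says how many nights enter the ANOVA, or how patients with fewer nights are handled.

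**The concern.** The design produces between one or two and seven nights per patient. The named method, in its classical form, works on a rectangular table of patients by nights, and a patient with an empty cell drops out. Over seven nights, the comparison meant to describe the whole admission would describe only patients who stayed at least a week.

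Two things are at stake. Patients who were measured and consented would contribute nothing to these outcomes. And the analysed group would be defined by length of stay, which is settled after the departments are randomised, so the protection of randomisation would then depend on discharge being unrelated to arm and to sleep.

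**Working it through.** **The plan's own figure.** None is given for the night-to-night outcomes. The stated 80% power belongs to the single-night primary comparison and is not in dispute. The design effect is 1 + (33 − 1) × 0.03 = 1.96. The standard error is 10.27 × √(2 × 1.96 / 99) = 2.04. The noncentrality is 7.7 / 2.04 ≈ 3.77, and with 4 degrees of freedom the power is 0.801.

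**How many patients would be complete?**

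Inputs from the protocol: 198 surgical and 198 medical patients, minimum stay one and two nights, ceiling seven nights.

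Assumption: a constant probability *h* of discharge after each night once the minimum stay is reached. The protocol gives no length of stay, so *h* is varied.

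Complete over seven nights = 198 × (1 − h)^6 + 198 × (1 − h)^5.

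| h | Surgical | Medical | Complete of 396 | Complete if only three nights entered |
|---|---|---|---|---|
| 0.10 | 198 × 0.531 | 198 × 0.590 | 222 (56%) | 339 |
| 0.15 | 198 × 0.377 | 198 × 0.444 | 163 (41%) | 311 |
| 0.20 | 198 × 0.262 | 198 × 0.328 | 117 (30%) | 285 |
| 0.30 | 198 × 0.118 | 198 × 0.168 | 57 (14%) | 236 |

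The last column is 198 × (1 − h)^2 + 198 × (1 − h). For the substudy (48 surgical and 48 medical patients), the seven-night formula gives about 54, 39, 28 and 14 of 96.

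**How many collected nights would go unused?** Expected nights per surgical patient are (1 − (1 − h)^7)/h, and per medical patient 1 + (1 − (1 − h)^6)/h. At h = 0.15 these are 4.53 and 5.15, so about 198 × 9.68 = 1,917 nights are collected. Complete patients hold 7 × 162.5 = 1,138 of them, so 41% are unused. The same steps give 28% at h = 0.10, 52% at 0.20 and 71% at 0.30.

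**Does the method really refuse unequal series?** A standard repeated-measures ANOVA routine, given 40 simulated patients with stays of one to seven nights, stopped because the data were unbalanced. Three of the 40 had all seven nights. A mixed model used all 40.

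**Is the arm difference biased?** This was simulated with a true difference of 7.7, SD 10.27, within-patient correlation 0.5 (assumed), base discharge probability 0.20 after every night (assumed) and no department effect. The odds of discharge are multiplied by exp(b) for each SD of better sleep the night before.

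| b | Complete, control | Complete, intervention | Complete-case difference |
|---|---|---|---|
| 0 | 26% | 26% | 7.7 |
| 0.25 | 26% | 21% | 7.4 |
| 0.5 | 26% | 16% | 6.9 |
| 1 | 25% | 11% | 5.2 |

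In 150 simulated trials of 396 patients at b = 0.5, the complete-case estimate averaged 6.7 (SD 1.5). A mixed model on all observed nights averaged 7.6 (SD 0.8).

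**The case against.** The protocol never says that incomplete patients are dropped, nor that all seven nights enter one ANOVA. Section 10.2 names a method in one sentence without model terms. A statistical analysis plan may add the detail, and some authors use the term loosely for a mixed model, which would escape the problem. If only the first three nights were used, 236 to 339 of 396 patients would remain for h from 0.30 to 0.10. This stands as a limit on how firmly the loss can be stated. It does not remove the mismatch: read in its ordinary sense, the named method does not fit the measurement rule, and a three-night analysis would not answer an objective that runs to seven nights.

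A patient with one night has no night-to-night change under any method. That is true of change, but such a patient still informs the average level, which the first secondary objective also asks about.

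A reader might go further and infer that the analysis would rest on the sickest patients, that most collected nights would be thrown away, or that the arms would be biased. The documents do not support these readings. Nothing links long stay to severity, and ASA 4 or higher and planned ICU admission are excluded. At h = 0.10 or 0.15, less than half of the nights go unused. With discharge unrelated to sleep or arm, the complete-case difference is unbiased.

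**Conclusion.** The point holds as a mismatch between method and design in the secondary night-to-night outcomes. Used classically over seven nights, the named ANOVA would keep about 222 down to 57 of 396 patients for assumed nightly discharge of 10% to 30%. Those figures rest on a constant discharge rate and would change with the true length-of-stay distribution, which the protocol does not give.

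Loss of precision and restriction to long stays follow from the method itself. Distortion of the arm comparison is conditional: in the scenarios tried, the difference shrank from 7.7 to between 7.4 and 5.2, and only where better sleep hastened discharge. The primary outcome uses one night and is untouched, so this is a correction that should be made rather than a threat to the trial's main result.

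**What to change.** Replace the three ANOVA sentences in section 10.2 with one linear mixed model on all observed nights:

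- Fixed effects: arm, night, arm-by-night and medical/surgical stratum.
- Random effects: patient and department.
- Small-sample degrees of freedom (for example Kenward-Roger), because there are only 12 departments.
- Results: arm difference per night and averaged over nights.

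Add three statements. First, the estimand is sleep while in hospital. Second, the model assumes that discharge is missing at random given the observed data, so late-night contrasts rest on few patients and on that assumption. Third, the number of patients observed will be reported by night and arm.

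Add a sensitivity analysis limited to the early nights that most patients share. If a mixed model was always intended, the wording should say so.

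The cost is a wording change. The data are already collected under the current procedures.

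### Two secondary objectives ask for a comparison of arms, but section 10.2 assigns each a paired hospital-versus-home t-test and plans no test of the arm difference

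*Protocol*

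**What the plan says.** The Secondary Objectives set two questions about the effect of the intervention. The first reads "To investigate whether the WEsleep interventions reduced the lowering of subjective sleep quality during admission when compared to subjective sleep quality before admission". The second concerns the phase shift in midpoint of sleep and asks whether it "was smaller for patients in the intervention group on the first postoperative night for surgical patients", with the second night of admission as the matching night for medical patients.

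Section 10.2, Secondary study parameter(s), gives the analyses. The first endpoint is described as "Difference in subjective sleep quality between hospital and at home". The second is assessed by "comparing midpoint of sleep during admission with midpoint of sleep on a work-free day before admission". Both bullets end with the same sentence: "To compare this a paired t-test with a significance level of 0.05 will be performed". Neither bullet mentions intervention or control.

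Other endpoints in the same section do name the arms. For 30-day mortality it says "This will be compared between the intervention and control group by performing a Chi-square test", and delirium and surgical site infection are treated alike. In the objective sleep substudy, sleep efficiency and sleep-wake timing each get an unpaired two-sided t-test of intervention against control.

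**The concern.** A paired t-test on home and hospital values tests whether the mean within-patient change is zero. The objectives ask whether that change differs between arms. These are different hypotheses, and the first can be clearly false while the second is true.

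The Introduction says the group has already shown that admission and surgery reduce sleep quality, so some hospital-versus-home difference is to be expected in both arms. If the plan is followed literally, two objectives about the intervention will be reported with p-values that mainly reflect being in hospital. A reader, or the trial team, could take such a p-value as evidence about the intervention. If the test is run in each arm, they could treat significance in one arm only as a comparison, which it is not.

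**Working it through.** The protocol gives no sample size or power for these two endpoints, so there is no planned figure to reproduce.

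**1. Objective against test**

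| | Objective asks | Planned test examines |
|---|---|---|
| Loss of sleep quality | Is the home-to-hospital drop smaller with the intervention? | Is the mean hospital-minus-home change zero? |
| Phase shift | Is the shift smaller with the intervention? | Is the mean admission-minus-home midpoint change zero? |

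The arms consist of different patients in different departments, so the pairing cannot be between arms. It can only be home with hospital in the same patient. The sentence in section 10 on evaluating confounding by linear regression names no endpoint and supplies no arm contrast for these two.

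**2. How often the paired test is significant when the intervention does nothing (RCSQ)**

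Inputs:
- n per arm = 6 departments × 33 = 198 (Study Design).
- SD of RCSQ = 10.27 (sample size section).
- Home-hospital correlation r = 0.3 to 0.5: assumed, not in the protocol.
- True drop, identical in both arms, of 1, 2 or 5 points: assumed, not in the protocol.

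SD of change = 10.27 × √(2(1 − r)), which is 12.15 at r = 0.3 and 10.27 at r = 0.5. SE = SD of change / √198, which is 0.864 and 0.730.

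The rejection probability within one arm (two-sided 0.05, normal approximation) is Φ(drop/SE − 1.96):

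| Drop | r = 0.3 | r = 0.5 |
|---|---|---|
| 1 point | Φ(1.16 − 1.96) = 21% | Φ(1.37 − 1.96) = 28% |
| 2 points | Φ(2.32 − 1.96) = 64% | Φ(2.74 − 1.96) = 78% |
| 5 points | Φ(5.79 − 1.96) > 99.9% | Φ(6.85 − 1.96) > 99.9% |

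With a larger SD of change, the 5-point figure falls to 99.7% (SD 15) and 94% (SD 20).

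**3. Paired and between-arm tests on the same data**

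This is a simulation of 2,000 runs with 198 patients per arm, SD of change 10.27, 15 and 20, and no clustering. It only shows which hypothesis each test addresses.
- Mean change −10 in both arms (no intervention effect): the pooled paired test rejects in 100% of runs. The comparison of changes between arms rejects in 4.3% to 6.2%, close to the nominal 5%.
- Control −3.85, intervention +3.85 (a difference of 7.7, the size used to plan the primary outcome): the pooled paired test rejects in 3.3% to 5.3% of runs. The between-arm comparison rejects in 96.7% to 100%.

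The pooled paired test thus follows the overall home-to-hospital change and misses the arm difference. Clustering by department would lower the power of the between-arm comparison.

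**The case against.** The strongest objections concern how far the point reaches.

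- **Per-arm tests are not empty.** A reader might infer that the planned test carries no information about the arms however it is run. That is true only of the pooled test. Run in each arm, it yields each arm's mean change and standard error, and the difference is a subtraction. What is missing is a planned test and interval for that difference. This part of the objection stands.
- **A significant result is not bound to occur.** A reader might infer that the paired test will almost certainly be significant. The protocol gives no home RCSQ and no size of drop; the Introduction states only a direction. The rate runs from about one in five to near certainty over drops of 1 to 5 points. No rate can be given for phase shift, because the protocol has no SD or expected shift for it.
- **An absolute phase shift is not required.** Signed advances and delays can cancel: half the patients at +1 h and half at −1 h average zero. But a smaller shift can mean a smaller mean delay or a smaller absolute deviation, and nothing in the protocol shows that shifts go both ways equally. It is fair to ask for the meaning to be stated, but not to prescribe the absolute value.
- **These are secondary endpoints.** They are two of nine main-study secondary objectives, and section 10.1 gives the primary endpoint its own between-arm test. This limits the severity.

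A statistical analysis plan that is not shown does not answer the core point. The protocol names the test, and the test does not fit the objective.

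**Conclusion.** The mismatch holds. Followed as written, section 10.2 tests neither objective: the stated analysis is hospital versus home, and no planned analysis estimates or tests the difference between arms in the loss of sleep quality or in phase shift.

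This conclusion rests on setting the objectives beside the tests and needs no assumed figure. The rates of 21–28%, 64–78% and over 99.9% only show how easily a paired test can be significant without an intervention effect. They rest on the assumed drops and correlations, on the protocol's SD of 10.27 applying to both home and hospital values, and on ignoring clustering.

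The point should be fixed but is not critical. It could mislead on two secondary objectives. A reader might infer that it also undermines the trial's main conclusion; it does not, because the primary comparison does not use these tests.

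**What to change.** In section 10.2, replace both paired t-tests with a between-arm comparison of the individual change (hospital minus home):

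- Adjust for medical/surgical stratum and allow for department clustering, with degrees of freedom based on the number of departments. With 12 departments and terms for intercept, arm and stratum, that is 12 − 3 = 9.
- Report the arm difference with its 95% CI.
- For phase shift, use the night named in the Secondary Objectives. For the RCSQ change, state which night or nights are used, since that objective refers only to the admission as a whole.
- State whether a smaller phase shift means the signed or the absolute shift.
- Keep the paired tests, if wanted, as descriptive within-arm results.
- Note as a limitation that home values are recalled at inclusion, after departments were allocated, so they are not a pre-randomisation baseline.

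The cost is a few sentences in the protocol. Home and hospital values are already collected, so no extra data or patients are needed.
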